## Abstract

**Background**: Determining the optimal resection line for an organ that cannot be palpated is crucial, but challenging, in minimally invasive gastrointestinal (GI) surgery. Therefore, there is an urgent need to establish the most effective method for tumor localization. We hypothesize that our novel near-infrared (NIR) fluorescence detection system will enable the highly accurate detection of fluorescent clips marking GI cancer. **Methods**: Twenty-five patients with gastric cancer, esophagogastric junctional cancer, or esophageal cancer will be enrolled. NIR fluorescent clips will be placed endoscopically around the tumor on the day before surgery. Patients in whom clip dislodgement is confirmed by preoperative abdominal radiography will be excluded. The clips will be placed before the transection of the organ, and those on the surgical specimen will be observed after transection using both the novel NIR fluorescence detection system and an existing NIR fluorescence imaging system. The detection rate and time, the fluorescence intensity, surgical margins, and adverse events will be evaluated. This study has been registered in the Japan Registry of Clinical Trials, with the code jRCTs012240043. (**Expected**) **Results**: As the novel fluorescence detection system allows for higher-sensitivity detection by analyzing the spectral characteristics of fluorescence and measuring the peak values, we anticipate that this new system will detect the fluorescent clips with high accuracy. **Conclusions**: This study aims to establish a novel tumor-marking method using fluorescent clips and a new detection system that can be easily applied in various medical facilities.

## 1. Introduction

Minimally invasive surgery (MIS) for gastric and esophageal cancer is widely accepted worldwide, and most gastrectomies and esophagectomies are performed entirely under laparoscopic and thoracoscopic guidance, including robotic surgery [1,2,3,4]. Although it is important to determine the precise incision line of the organ intraoperatively for upper gastrointestinal (GI) surgery, it is generally difficult to confirm the location of the tumor without palpation, especially in early-stage cancer, during MIS. The optimal resection of the organ prevents not only non-curative resection with insufficient surgical margins but also troublesome anastomosis involving a highly resected esophagus in the mediastinum [5,6]. Moreover, an unnecessary total gastrectomy or the excessive resection of the stomach wall can result in reduced food intake and postoperative weight loss [7,8].

Although methods such as ink tattooing, endoscopic clipping, and intraoperative endoscopy are currently available to identify tumor locations during surgery, the dissemination of ink into the wall complicates the determination of both the precise incision line of the organ and the dissectable layer of the adjacent tissue [9,10]. Regarding endoscopic clip marking, surgeons may have difficulty detecting it without significant experience using a laparoscopic ultrasound probe due to the small size of the clips. Although intraoperative endoscopy is the most reliable method to identify the location of the tumor, it can lead to increased medical costs and prolonged operation times, owing to the need for securing an endoscopist and using multiple pieces of equipment.

Recent reports describe a tumor-marking method that uses an endoscopic clip labeled with near-infrared (NIR) fluorescence, matching almost the same wavelength as indocyanine green (ICG), alongside an NIR fluorescence imaging system [11,12,13,14,15,16]. While this method enables the accurate and rapid intraoperative identification of the tumor location and resection lines, the clips may sometimes go undetected by the existing imaging system. This problem arises because NIR light can penetrate tissue only up to 5–8 mm, depending on the thickness of the gastric or esophageal wall and the tumor’s location [17]. Even when the clips are detectable, various adjustments are often required, such as placing the clips on the anterior wall regardless of the tumor’s location, expanding the gastric wall with forceps, releasing the omentum, and inverting the stomach to enable observation from the posterior wall. These procedural modifications can also contribute to prolonged operative periods. We developed a novel NIR fluorescence detection system, Lumifinder™ (Advantest Co, Tokyo, Japan), which may address the limitations of the current imaging systems [18]. This system successfully enabled the detection of fluorescent clips in the porcine stomach, which typically has a thicker wall than the human stomach. In this study, we hypothesized that our novel NIR fluorescence detection system would enable the highly accurate detection of fluorescent clips at any location in the stomach and esophagus.

## 2. Materials and Methods

### 2.1. Study Design

This is a single-center, open, interventional, and exploratory prospective clinical trial. This study has been registered in the Japan Registry of Clinical Trials, with the code jRCTs012240043 (https://jrct.niph.go.jp/en-latest-detail/jRCTs012240043) (accessed on 18 October 2024).

The detailed schedule and schema are presented in Figure 1 and Figure 2, respectively. All research subjects will be registered until 31 March 2026. The collected data will be analyzed up until 31 March 2027. The data will also be stored and may be utilized in future studies.

#### 2.1.1. Preoperative Procedures

NIR fluorescence clips are placed endoscopically by an endoscopist 24 h before surgery, as follows:i.Distal gastrectomy, total gastrectomy, and esophagectomy: place two clips on the oral side of the tumor.ii.Proximal gastrectomy: place two clips on the oral side and two clips on the anal side of the tumor.
An abdominal X-ray is examined to confirm the location of the clips.

#### 2.1.2. Intraoperative Procedures

Immediately after initiating laparoscopic, thoracoscopic, or robotic procedures, the surgeon uses the NIR fluorescence detection system to locate the NIR fluorescent clips on the target organ. The probe tip should be positioned 4 cm from the target organ and applied as perpendicularly as possible to the organ in order to excite and detect the fluorescence of the clips. The quantification of the fluorescence of the clips and the measurement of the detection time are recorded.As a reference, the NIR fluorescent clips are examined using an existing NIR fluorescence imaging system. In laparoscopic and thoracoscopic surgery, the endoscope is equipped with a fluorescence observation mode. This endoscope is also used in robotic surgery for fluorescence observation, allowing the study to be conducted under similar conditions.If the fluorescent clip cannot be detected, the endoscopist performs an additional intraoperative oral endoscopy.After these examinations, the gastric cancer, esophagogastric junctional cancer, or esophageal cancer is resected in the usual manner.

#### 2.1.3. Postoperative Procedures

The NIR fluorescence of the clips is observed and quantified by the NIR fluorescence detection system in the surgical specimen.During the 1–2 weeks following surgery, the patient’s overall condition and any adverse events are monitored through clinical observation, blood tests, and chest and abdominal X-rays, as appropriate.

### 2.2. Materials and Equipment

#### 2.2.1. Novel Laparoscopic Near-Infrared Fluorescence Spectrum System (Lumifinder™)

The Lumifinder™ has been extensively described in previous studies [18]. The system utilizes a laser diode with a wavelength of 785 nm and a maximum output power of 5 mW as the excitation source. For irradiation, the laser beam is directed onto the central region of a fused-silica coaxial fiber configured in a Y-shape. The near-infrared (NIR) fluorescence emitted by the NIR fluorescent clips is gathered through the outer segment of the coaxial fiber and analyzed using spectroscopy. Since the fluorescence peaks at around 840 nm—close to the excitation wavelength of 785 nm—a narrowband notch filter is placed at the entrance of the spectroscope to suppress signals from the excitation source (Figure 3). The probe (diameter = 10 mm, length = 350 mm) can be inserted through a 12 mm port into either the abdominal or thoracic cavity. The fluorescence of the NIR fluorescent clip is excited by the excitation light source from the probe tip close to the target organ. The wavelength graph is described and recorded on the system when fluorescence is detected.

#### 2.2.2. Endoscopic NIR Fluorescence Imaging System

We will utilize the VISERA ELITE 2 system (Olympus Co., Tokyo, Japan), which activates ICG with emitted light at a wavelength of 760 nm, enabling both intraoperative white light imaging and NIR fluorescence visualization following exploration with Lumifinder™ during laparoscopy, thoracoscopy, and robotic surgery.

#### 2.2.3. The Fluorescent Clip (XEMEX FS Marker^®^)

The XEMEX FS Marker^®^ (Zeon Medical Co., Tokyo, Japan) has near-infrared fluorescent resin applied to its arms, which hold the GI mucosa and absorb and emit the near-infrared fluorescence with peaks of 760 and 790 nm, respectively (Figure 4). This clip has been approved for clinical use (registration number: 30500BZX00292000).

#### 2.2.4. Endpoints

The primary endpoint of this study is to determine whether the Lumifinder™ can detect the XEMEX FS Marker^®^ around the tumor. Secondary endpoints include assessing the variation in signal intensity at different tumor locations, differences in the thickness of the gastric or esophageal wall, the time required for clip identification and fluorescence measurement, and the measurement of the proximal and distal margins of the surgical specimen. The safety endpoint involves evaluating any adverse events associated with the use of Lumifinder™ and the XEMEX FS Marker ^®^.

#### 2.2.5. Study Patients and Eligibility Criteria

This study will include patients diagnosed with gastric, esophagogastric junction, or esophageal cancer who are either visiting or have been admitted to the Department of Gastroenterological Surgery II at Hokkaido University Hospital and are considered eligible for surgery by the department. The eligibility criteria are listed in Table 1. The principal investigator and sub-investigator will provide a detailed explanation of the study to the patients at the Department. If the patients agree to participate, informed consent will be obtained using a dedicated consent form approved by the Research Ethics Board of Hokkaido University Hospital.

#### 2.2.6. Target Number of Patients

Twenty-five patients will be enrolled prospectively. We will recruit participants from 1 February 2025, to 31 March 2026. Given that a total of 50 or more patients meet the eligibility criteria annually in our department, it is anticipated that the target number will be achieved within one year.

#### 2.2.7. The Determination of the Sample Size

The target sample size was set to 25 cases to account for potential clip dislodgement and ineligible cases. This determination was based on calculations using the Wilson’s score method, which indicated that 21 cases would be required to achieve a width of less than 30% for the 95% confidence interval, assuming a success rate of 90% for the fluorescence measurement and the position identification of the XEMEX FS marker using Lumifinder™, with a probability of 80% or higher. This was determined in collaboration with the statistician responsible for the statistical analysis at the Data Science Center, the Institute for Medical and Health Science Research Development, Hokkaido University Hospital.

#### 2.2.8. Statistical Analysis Methods

The patients’ demographic and baseline characteristics will be described using appropriate statistical measures: the mean and the standard deviation or the median and the interquartile range, as needed, for the continuous data and the frequency with the percentage for the categorical data. For the primary endpoint, the success rate and a 95% confidence interval will be calculated using the Wilson’s score method. The secondary endpoints will be analyzed by estimating values with corresponding 95% confidence intervals, and the relationships among the variables will be assessed using visual and statistical tools such as scatter plots, box plots, and Pearson’s correlation coefficients, among others, as appropriate. Cases in which all the clips are confirmed to have been dislodged during preoperative abdominal radiographs or intraoperative evaluations will be excluded from the statistical analysis.

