#### 2.2.9. Anticipated Benefits and Disadvantages (Burdens and Risks)

Anticipated benefits: determining the optimal resection line using fluorescent clip markings may contribute to improved curability and the maintenance of postoperative function, including food intake.Anticipated disadvantages: The preoperative oral endoscopic marking and the intraoperative fluorescence measurement performed for research purposes will each involve a time commitment of approximately 30 min. Adverse events such as perforation, bleeding, tissue damage, and infection are mentioned in the package inserts of the Zemex FS Marker and Lumifinder™. However, the likelihood of such adverse events occurring owing to the use of these devices is extremely low, provided that endoscopic procedures and clipping are performed by endoscopy specialists and that the maintenance, cleaning, disinfection, and sterilization of the equipment and scope are conducted properly. If the fluorescent clip cannot be detected or is dislodged during surgery, additional intraoperative oral endoscopy may be required to determine the organ resection line, and the prohibition of MRI imaging after clip marking, as stated in the package insert, could potentially disadvantage the study participants.

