#### 2.2.10. Handling of Adverse Events

Adverse events are any unfavorable or unintended injuries or symptoms (including abnormal clinical laboratory values) that occur in a research subject, whether or not they are related to the research that has been conducted, and that are recognized during the observation period from the day before the surgery marking.

When the investigator recognizes an adverse event, they will immediately take appropriate measures and provide treatment. The name of the adverse event, the date of onset and the date of resolution, the severity (mild, moderate, or severe), the outcome, the causal relationship with the study (related, unrelated), and the course of the event will be recorded. In addition, if the research device is discontinued or treatment for the adverse event is required, the research subject will be informed accordingly.

If the doctor in charge of the research becomes aware of the occurrence of any serious adverse event (death, life-threatening conditions, hospitalization or the prolongation of hospitalization, persistent or significant disability/incapacity, and any congenital anomaly in offspring), he/she shall take necessary measures, such as providing an explanation to the research subject and promptly reporting the event to the principal investigator. The principal investigator shall promptly report the event to the administrator of the medical institution of the relevant organization, take appropriate measures, and share information with the sub-investigator.

If an event that meets the conditions for an important adverse event (eczema, nausea, vomiting, etc., associated with fluorescent clip marking) occurs, the principal investigator will promptly report it, following the procedure for reporting serious adverse events. The principal or sub-investigator will appropriately record other adverse events in the medical record. 

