#### 2.2.11. The Discontinuation or Termination of the Study

If a subject falls into any of the categories listed below, the principal investigator will promptly discontinue the subject’s participation in the study and take appropriate measures. Additionally, the investigator will monitor any adverse events identified during discontinuation and ensure the subject’s safety by performing necessary examinations and tests and providing appropriate medical care, contingent on the subject’s cooperation. The examinations conducted during discontinuation will be limited to those deemed medically relevant, respecting the subject’s autonomy and informed consent. Data relevant to the study will be collected promptly upon discontinuing the subject’s participation. In cases where a subject ceases to attend scheduled visits during the research period, the principal investigator will attempt to contact the subject via telephone or other means to encourage them to return for follow-up. If the subject cannot return to the hospital, their health condition will be assessed remotely through verbal communication. Any adverse events will be managed according to the relevant section’s protocol. The date and reason for discontinuation will be recorded in the Electronic Data Capture (EDC) system. The date of discontinuation will be defined as the date on which the principal investigator decides to terminate the subject’s participation in the study. The following are the criteria for discontinuation:Subject requests treatment modification or discontinuation—to uphold ethical considerations and respect for the subject’s autonomy.Observation of an adverse event that precludes continued participation—based on safety concerns.Occurrence of death or a life-threatening condition—to prioritize subject safety.Worsening of the primary disease—for the subject’s safety and well-being.Discovery of pregnancy—to mitigate the risks associated with potential harm to the subject or fetus.Deviation from the selection criteria or the violation of the exclusion criteria—to maintain the study’s integrity and validity.Failure to attend scheduled hospital visits—when continued participation cannot be assured.Confirmation of clip displacement via preoperative abdominal X-ray or intraoperative observation—rendering study continuation unfeasible.Other reasons deemed inappropriate by the principal investigator—based on professional judgment.

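### The exclusion of patients who lost all clips is not limited to the detection analyses, so as worded it also removes marked patients from the safety endpoint

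*Protocol article*

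**What the plan says.** Section 2.2.8 (Statistical Analysis Methods) covers baseline summaries, the primary success rate and the secondary endpoints. It closes with a rule for patients found, on the preoperative X-ray or during surgery, to have lost every clip: they "will be excluded from the statistical analysis". No endpoint is named as the limit of that rule.

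Two other places deal with lost clips in looser terms:

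- Abstract: "Patients in whom clip dislodgement is confirmed by preoperative abdominal radiography will be excluded". It does not say whether one lost clip is enough, and it does not mention findings during surgery.
- Section 2.2.11, as a criterion for ending a subject's participation: "Confirmation of clip displacement via preoperative abdominal X-ray or intraoperative observation". Again it does not require that all clips are lost.

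On safety, Section 2.2.4 states: "The safety endpoint involves evaluating any adverse events associated with the use of" Lumifinder and the XEMEX FS Marker. Section 2.2.10 starts adverse event observation at the marking on the day before surgery. For each event it records, among other items, "the causal relationship with the study (related, unrelated". Section 2.2.11 adds that for discontinued subjects "the investigator will monitor any adverse events identified during discontinuation".

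**The concern.** For detection, the exclusion is understandable: with no clip in place there is nothing for the probe to find. That reason does not carry over to safety. A patient whose clips have all come off has still been exposed to the marking endoscopy and to the clip. If the loss is discovered during surgery, the patient may also have been probed, because Section 2.1.2 has probing begin as soon as the minimally invasive procedure starts. Section 2.2.9 names the harms in view: "Adverse events such as perforation, bleeding, tissue damage, and infection are mentioned in the package inserts" of the two devices.

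At stake is the denominator, and possibly the numerator, of the safety result. Under the rule as written, clip safety would be summarised in patients who kept at least one clip, not in all patients who were marked. In a single-arm study of 25 patients, one event more or less is visible in the result.

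**Working it through.** **1. Does any passage limit the exclusion, or keep these patients in for safety?**

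| Place | What it does with patients who lost clips | Limited to detection? |
|---|---|---|
| Abstract | Excludes on preoperative radiography | No |
| Section 2.2.8 | Removes from the analysis if all clips are lost | No |
| Section 2.2.11 | Ends participation; adverse events still monitored | Not addressed |
| Section 2.2.10 | Records events in any research subject from the marking on | Not addressed |

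None does. The events are collected, but the only stated analysis rule leaves the patients out.

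**2. The three wordings differ.** Section 2.1.1 places two clips, or four for proximal gastrectomy. A patient who loses one of two stays in the analysis under Section 2.2.8. On a literal reading of the Abstract (if the loss is seen on the X-ray) or of Section 2.2.11, the same patient could be excluded or discontinued. The three passages must be reconciled.

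**3. The plan's own figure.** Section 2.2.7 asks for 21 evaluable patients, so that the Wilson 95% interval is narrower than 30 percentage points with probability at least 80% when the true success rate is 90%.

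- Wilson width = 2z·√[p(1−p)/n + z²/(4n²)] / (1 + z²/n), with z = 1.96.
- For n = 21, 18 successes give a width of 0.297 and 17 give 0.323, so at least 18 are needed. With X binomial (21, 0.9), P(X ≥ 18) = 0.848.
- For n = 20, at least 18 are again needed, and the probability is 0.677.

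The figure of 21 reproduces. The enrolment margin is 25 − 21 = 4, or 4/25 = 16%. Section 2.2.7 gives it as an allowance for lost clips and for ineligible patients together. It gives no split and no upper limit.

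**4. Illustration of the effect on safety.** The number m of marked patients who lose all clips is an assumption. It is shown from 0 to 4 because that is the enrolment margin, and all 25 are taken as marked. With zero events, the exact (Clopper-Pearson) upper limit of the two-sided 95% interval is 1 − 0.025^(1/n), with n = 25 − m.

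| m excluded | n analysed | Upper limit, zero events |
|---|---|---|
| 0 | 25 | 13.7% |
| 1 | 24 | 14.2% |
| 2 | 23 | 14.8% |
| 3 | 22 | 15.4% |
| 4 | 21 | 16.1% |

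Now take m = 4 and suppose the only clip-related events occur among those four. The analysis as worded shows 0/21 = 0% in every case. The marked cohort shows 1/25 = 4%, 2/25 = 8%, 3/25 = 12% or 4/25 = 16% for one, two, three or four affected patients.

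**5. The two devices have different exposed groups.** Patients discontinued on the preoperative X-ray had the clip but no Lumifinder. They belong in the clip denominator and not in the Lumifinder one.

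**The case against.** The best defence is that Section 2.2.8 describes no safety analysis. On that view, the closing sentence refers only to the analyses just listed, while safety is named separately in Section 2.2.4 and handled in Section 2.2.10. A statistical analysis plan exists or is planned (Section 2.2.13) and may define a safety set. This reading is possible, and the absence of a safety-set definition from an article would not itself be a fault. But nothing in the text states the narrower reading. The point concerns a rule the article does fix: a plan that kept these patients for safety would depart from the sentence as published.

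Several stronger readings are tempting, and the documents do not support them:

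- *That adverse events in these patients go unrecorded.* They do not. Sections 2.2.10 and 2.2.11 still require recording, monitoring and prompt reporting of serious events.
- *That losing any clip removes a patient from the analysis.* Section 2.2.8 requires that all clips are lost.
- *That the plan permits up to 4 exclusions.* Section 2.2.7 sets no cap, and its margin also covers ineligible patients.
- *That clip loss signals mucosal injury, so that the exclusion is tied to the safety outcome.* Section 2.2.9 lists bleeding and tissue damage but does not link them to dislodgement.
- *That safety cannot be tabulated by device because relatedness is recorded once, against the study.* Section 2.2.4 does not promise separate rates. Onset date and course are recorded, so an event that starts before surgery can be placed with the marking. The case report form, which is not shown, may hold more detail. Postoperative events would be harder to separate, so a finer item would help, but its absence is not an error.

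**Conclusion.** The point holds as a defect of wording. Applied literally, the exclusion in Section 2.2.8 takes patients exposed to clip marking, and possibly to Lumifinder, out of the analysis of the safety endpoint in Section 2.2.4, although their events are collected.

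The effect on precision is modest: within the enrolment margin, the zero-event upper limit rises from 13.7% to at most 16.1%. The effect on the observed rate depends on whether any event falls among the excluded patients, which the documents cannot tell us. Both figures rest on the assumed number of total clip losses. Severity is minor to moderate: the trial is exploratory, and the primary endpoint, its Wilson interval and the sample size of 21 from 25 do not change.

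**What to change.** 1. In Section 2.2.8, state that the exclusion for loss of all clips applies only to the detection and fluorescence analyses.
2. In the same place, state that clip and marking adverse events are reported in all patients in whom clip placement was attempted, and Lumifinder adverse events in all patients who were probed.
3. Reconcile the Abstract and Section 2.2.11 with Section 2.2.8 on whether the trigger is loss of any clip or of all clips, and on whether it covers findings during surgery.
4. Optionally, record relatedness separately for clip/marking and for Lumifinder, since the single item in Section 2.2.10 does not distinguish them.

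Items 1 to 3 cost a few sentences, with no added patients and no change to the sample size. Item 4 adds a field or two to the case report form, unless it already has them, and is best in place before or early in enrolment, because attribution is most reliable when made as events occur.
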